**4.3 Data Monitoring**

An independent Data Safety Monitoring Board (DSMB), consisting of experts in clinical research, in haematology and in statistics/methodology, will be established before patient enrolment. The DSMB Charter will be prepared by the SC and signed by the members of the DSMB before the trial commences. The DSMB will have access to the summary of all results and will consider the appropriateness of the sample size, of the efficiency and of the quality of the data collection system, and eventual occurrence of suspected protocol-related adverse events. The DSMB will have the right to stop the trial for safety reasons.

**4.4 Analyses ad interim**

Considering the statistical approach, an interim analysis is planned after the randomisation of 150 patients (50% of sample size) for the double objective of monitoring safety and verifying the accuracy of the assumptions made for sample size estimation, regarding the event rate of the primary outcome in relation to the anticipated survival benefit. With the interim analysis we will be able to evaluate whether the data suggests that there is substantial superiority of one treatment. The obtained results will be evaluated by the DSMB and by the SC and, in case of significant differences in survival among the groups, all patients will be switched to the most promising treatment.

1. **SAFETY CRITERIA EVALUATION**
   1. **Safety profile**

Data on safety profile, nature, incidence and severity of adverse events (AEs) and serious adverse events (SAEs) will be collected. Any reason for drug interruption, reduction and discontinuation will be collected. Toxicities will be graded using NCI Common Terminology Criteria for adverse Events (CTCAE) version 4.03.

- 1. **Adverse events (AE) and serious adverse events (SAE)**

The investigator is responsible for the detection and documentation of AE and SAE events, according to the criteria defined in this protocol. During the safety evaluation, the Investigator or site staff will be responsible for detecting, documenting and reporting AEs and SAEs, as detailed in both this section of the protocol and in the AE/SAE section of the CRF.

- - 1. **Definition of an AE**

An AE is defined as any untoward medical occurrence in a patient, temporarily associated with the use of a medicinal product, whether or not it is considered related to the medicinal product. An AE can therefore be any unfavourable and unintended sign (including an abnormal laboratory finding), symptom, or disease (new or exacerbated) temporarily associated with the use of a medicinal product. For marketed medicinal products, this also includes failure to produce expected benefits (i.e. lack of efficacy), abuse or misuse.

Examples of an AE include:

- Significant or unexpected worsening or exacerbation of the condition/indication under study.
- Exacerbation of a chronic or intermittent pre-existing condition including either an increase in frequency and/or intensity of the condition.
- New conditions detected or diagnosed after investigational product administration even though it may have been present prior to the start of the study.
- Signs, symptoms, or the clinical sequelae of a suspected interaction.
- Signs, symptoms, or the clinical sequelae of a suspected overdose of either investigational product or a concurrent medication (overdose per se should not be reported as an AE/SAE).

Examples of an AE do not include:

- Medical or surgical procedure (e.g., endoscopy, appendectomy); the condition that leads to the procedure is an AE.
- Situations where an untoward medical occurrence did not occur (social and/or convenience admission to a hospital).
  - 1. **Definition of an SAE**

An SAE is defined as any untoward medical occurrence that, at any dose:

1. Results in death
2. Is life-threatening

Note: The term 'life-threatening' in the definition of 'serious', refers to an event in which the subject was at risk of death at the time of the event. It does not refer to an event, which hypothetically might have caused death, if it were more severe.

1. Requires hospitalization or prolongation of existing hospitalization

Note: In general, hospitalization signifies that the subject has been detained (usually involving at least an overnight stay) at the hospital or emergency ward for observation and/or treatment that would not have been appropriate in the physician’s office or in an outpatient setting. Complications that occur during hospitalization are AEs. If a complication prolongs hospitalization or fulfils any other serious criteria, the event is serious. When in doubt as to whether “hospitalization” occurred, or was necessary, the AE should be considered serious. Hospitalization for elective treatment of a pre-existing condition that did not worsen from the baseline is not considered an AE.

1. Results in disability/incapacity

Note: The term disability means a substantial disruption of a person’s ability to conduct normal life functions. This definition is not intended to include experiences of relatively minor medical significance such as uncomplicated headache, nausea, vomiting, diarrhoea, influenza, and accidental trauma (e.g. sprained ankle) which may interfere or prevent everyday life functions but do not constitute a substantial disruption.

1. Is a congenital anomaly/birth defect.

Medical or scientific judgement should be exercised in deciding whether reporting is appropriate in other situations, such as important medical events that may not be immediately life-threatening or result in death or hospitalization but may jeopardize the subject or may require medical or surgical intervention to prevent one of the other outcomes listed in the above definition. These should also be considered serious. Examples of such events are invasive or malignant cancers, intensive treatment in an emergency room or at home for allergic bronchospasm, blood dyscrasias or convulsions that do not result in hospitalization, or development of drug dependency or drug abuse.

- 1. **Recording of AEs and SAEs**

When an AE/SAE occurs, it is the responsibility of the investigator to review all documentation (e.g. hospital progress notes, laboratory, and diagnostics reports) relative to the event. The investigator will then record all relevant information regarding an AE or SAE on the eCRF. It is not acceptable for the investigator to send photocopies of the subject’s medical records in lieu of completion of the appropriate AE or SAE CRF pages. The investigator will attempt to establish a diagnosis of the event based on signs, symptoms, and/or other clinical information. In such cases, the diagnosis should be documented as the AE/SAE and not the individual signs/symptoms. Any AEs or SAEs occurring during the study must be documented in the subject's medical records and on the appropriate page of the eCRF. Each AE or SAE is to be recorded individually. All AEs which occur during the course of the study should be recorded in the eCRF. Information on the AE must be recorded on a specific AE form and forwarded to the DSMB. The SC and the DSMB will evaluate the adverse events occurred during the study.

- - 1. **Evaluating AEs and SAEs**
       1. **Assessment of intensity**

The investigator will make an assessment of intensity of each AE and SAE reported. In this protocol, the intensity of AEs and SAEs will be graded on a scale of 1 to 5 according the National Cancer Institute (NCI) Common Toxicity Criteria for Adverse Events (CTCAE) Version 4.03 and are available at [http://evs.nci.nih.gov/ftp1/CTCAE/CTCAE_4.03_2010-06- 14_QuickReference_5x7.pdf](http://evs.nci.nih.gov/ftp1/CTCAE/CTCAE_4.03_2010-06-%2014_QuickReference_5x7.pdf).

For SAEs, the maximum intensity (or grade) will be reported in the eCRF. For non-serious AEs, each change in intensity (or grade) will be reported in the eCRF.

- - - 1. **Assessment of causality**

The investigator is obliged to assess the relationship between the study medical product and the occurrence of each AE/SAE. The investigator will use clinical judgement to determine the relationship. Alternative causes, such as natural history of the underlying diseases, concomitant therapy, other risk factors, and the temporary relationship of the event to the study drugs will be considered and investigated. There may be situations when an SAE has occurred, and the investigator has minimal information to include in the initial report. However, it is very important that the investigator always makes an assessment of causality for every event prior to transmission of the SAE form to the Coordinating Centre. The investigator may change his/her opinion of causality in light of follow-up information, amending the SAE eCRF accordingly. The causality assessment is one of the criteria used when determining regulatory reporting requirements. The investigator will provide the assessment of causality as per instructions on the SAE form in the Investigators File.

- - - 1. **Follow-Up of AEs and SAEs**

After the initial AE/SAE report, the investigator is required to proactively follow each subject and provide further information on the subject’s condition. All AEs and SAEs documented at a previous visit/contact and are designated as ongoing, will be reviewed at subsequent visits/contacts. AEs that are ongoing with a toxicity of Grade 3 or 4, or have a relationship to study drug that is suspected (Reasonable Possibility) will be queried for resolution at study conclusion and at approximately 30 days after the last dose of study. Once resolved, the appropriate AE/SAE CRF page(s) will be updated. The investigator will ensure that follow-up includes any supplemental investigations as may be indicated to elucidate the nature and/or causality of the AE or SAE. This may include additional laboratory tests or investigations, or consultation with other health care professionals. New or updated information will be recorded on the originally completed SAE form in the Investigator’s File, with all changes signed and dated by the Investigator.

- 1. **Regulatory reporting requirements for adverse events**

The Principal Investigator at Coordinating Centre (CC) has a legal responsibility to notify, as appropriate, both the local regulatory authority and other regulatory agencies about the safety of a product under clinical investigation. Prompt notification of SAEs by the Investigator to the appropriate project contact for SAE receipt is essential so that legal obligations and ethical responsibilities towards the safety of other subjects are met. The Principal Investigator at CC, or responsible person according to local requirements, will comply with the applicable local regulatory requirements related to the reporting of SAEs to regulatory authorities and the Independent Ethics Committee (IEC). In particular, all the Suspected Unexpected Serious Adverse Reactions (SUSARs) that occur while on treatment and within 30 days since the last investigational drug administration, and that have a suspected relationship to study’s drug (Reasonable Possibility) will be notified with an urgency procedure to the local regulatory Agency (AIFA) and IEC with the following timelines:

- SUSARs that are considered life-threatening: notification within 7 days.
- SUSARs that are not considered life-threatening: notification within 15 days.

The notification with urgency procedure is not required for SAEs that are expected with the drugs used in the protocol, and for non-serious AEs, both expected and unexpected. For these events (expected SAEs and AEs), the CC will notify the local regulatory agency and IECs by an annual safety report. The CC is responsible for providing all the investigators involved in the trial with appropriate timelines, and all the safety information relevant for patient safety.

1. **ETHICS**

The study will be conducted in line with the protocol, the Declaration of Helsinki (1964) and subsequent amendments and updates (Fortaleza, Brazil, October 2013). Moreover, it is the responsibility of the investigator to ensure that the study will be done in line with the requirements of Good Clinical Practice (GCP) and the applicable regulatory requirements.

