**3.0 METHODS: ASSIGNEMENT OF INTERVENTIONS**

**3.1 Allocation and blinding**

Randomisation will be centrally performed by using a secure, web-based system, which will be developed by the Methodological and Statistical Unit at the Azienda Ospedaliero-Universitaria of Modena. Randomisation stratified by 4 factors: 1) Gender (M/F); 2) Age (<75/≥75 years); 3) BMI (<30/≥30); 4) Co-morbidities (0-1/>2) with random variable block sizes will be generated by STATA software. The web-based system will guarantee the allocation concealment. The physicians involved in the study, once they have obtained the patient’s consent, will connect to the website and will register the patient that meets inclusion criteria. The system will also allow the randomisation of the patient and the arm to which he/she is allocated will appear on the monitor. The physician who performed the randomisation will communicate which dose the patient will receive to the colleagues who are in charge of administering LMWH. The information collected during the patient follow-up will be entered on the website and stored on the Hospital’s server. The local coordinator will be in charge of training the personnel involved in the study according to what is stated in the protocol. The study is conceived as open label, i.e. the patients and all healthcare personnel will be aware of the group allocation.

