**6.2 Ethical conduct of the study**

The study was designed and will be implemented and performed in accordance with the ICH Harmonized Tripartite Guidelines for Good Clinical Practice, with applicable local regulations (including European Directive 2001/20/EC), and with the ethical principles laid down in the Declaration of Helsinki.

- 1. **Written informed consent**

The Investigator at each Centre will ensure that the subject is given full and adequate oral and written information about the nature, purpose, possible risks and benefits of the study. Subjects must also be notified that they are free to discontinue from the study at any time. The subject’s signed and dated informed consent must be obtained prior to conduct any procedure specific for the study. The original signed Written Informed Consent Form must be stored, and a copy must be given to the patient.

- 1. **Subject data protection**

The Written Informed Consent Form will explain that the study data will be stored on a centralised hospital server, maintaining confidentiality in accordance with national data legislation. The Investigator must ensure anonymity of the patients; all computer data will be identified by subject initial and number only. Enrolment log must be kept strictly confidential to enable patient identification at the site.

- 1. **Audits and inspections**

The Principal Investigator and the SC will provide all the necessary information and material to the participating centres in order to standardize all the protocol-related procedures and to avoid unexpected variability between centres. A preliminary audit between the CC and the satellite centres will be performed before starting the recruitment phase to offer as much consensus and homogeneity as possible. Printed and electronic informative material (complete original protocol, informed consent modules, informative modules for patients and relatives, recruitment checklist, graphic timeline of interventions and visits, order list for physicians and nurses) will be distributed to every Centre.

Source data/documents must be available to inspections by the designee or Health Authorities.

- 1. **Declaration of interest**

The study participants declare no financial and/or other conflicts of interest related to the study.

- 1. **Dissemination policy**

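### Section 4.4 has the Steering Committee, as well as the independent DSMB, evaluate between-arm interim results while up to half of this open-label trial is still to be randomised

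*Protocol*

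**What the plan says.** Protocol section 4.3 provides for independent oversight: "An independent Data Safety Monitoring Board (DSMB), consisting of experts in clinical research, in haematology and in statistics/methodology, will be established before patient enrolment". It gives the DSMB access to summary results, asks it to consider whether the sample size is appropriate, and has the SC prepare the DSMB Charter.

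Section 4.4 places a single interim analysis at 150 randomised patients, half of the 300 planned. It has two stated aims, safety monitoring and a check of the sample-size assumptions. It adds that the analysis will "evaluate whether the data suggests that there is substantial superiority of one treatment". On who sees the output it states: "The obtained results will be evaluated by the DSMB and by the SC". The same sentence continues: "in case of significant differences in survival among the groups, all patients will be switched to the most promising treatment".

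Other sections show what the SC does. Section 4.1 makes it the provider of the eCRF. The section on recording AEs and SAEs says: "The SC and the DSMB will evaluate the adverse events occurred during the study". The section on audits and inspections says: "The Principal Investigator and the SC will provide all the necessary information and material to the participating centres". Section 3.1 confirms that "the patients and all healthcare personnel will be aware of the group allocation".

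**The concern.** An independent monitoring board keeps emerging comparative results away from those who run a trial. Section 4.4 removes that separation for the SC, and it does so by a positive statement. This is not a detail left for the SAP. A Charter or SAP that restricted the SC's access would have to depart from the protocol sentence.

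Open-label treatment makes this more important. Clinicians know each patient's arm, but they do not otherwise know which arm is ahead across the ten sites. Anyone who learns the aggregate trend can apply it patient by patient. Three parts of the trial are open to that influence:

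- whom to enrol;
- the two ventilation components of the primary endpoint (section 2.4.1), which turn on a clinician's judgement of need;
- discontinuation of the assigned treatment, which the sections on treatment duration and on discontinuation leave partly to the physician or investigator.

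The SC's interest in the sample-size assumptions does not require by-arm data, because a pooled event rate would serve. The point is separate from the significance level used at the interim look.

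**Working it through.** The core of the check is textual. The arithmetic only shows how much of the trial lies beyond the interim look and whether a trend would be visible.

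**1. Are the results by arm?** Section 4.4 does not use the word unblinded. But superiority of one treatment cannot be judged, nor a survival difference between groups acted on, from pooled data. The object of the quoted sentence is therefore a between-arm comparison.

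**2. Does anything limit what the SC sees?** Section 4.3 gives the DSMB access to summary results but does not say that the access is exclusive. No section confines the SC to a recommendation or to pooled data.

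**3. Is the SC operational?** Sections 4.1 and 4.3, and the sections on AE recording and on audits and inspections, together give it data-capture, charter, safety-review and centre-support roles.

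**4. The plan's own figures.** Section 2.6 assumes 25% to 30% clinical worsening in controls, a 50% relative reduction, two-sided alpha 5%, power 80% and 1:1 allocation. The pooled-variance formula is n per arm = [1.960·√(2p̄(1−p̄)) + 0.842·√(p₁(1−p₁)+p₂(1−p₂))]² / (p₁−p₂)².

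- 25% versus 12.5%: 152 per arm, 304 in total, which reproduces the stated 300 within rounding.
- 30% versus 15%: 121 per arm, 242 in total.

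**5. Patients still to be randomised.** 300 − 150 = 150, or 50%. Section 2.7 gives 40 eligible per month × 80% = 32 enrolled per month. At that rate 300/32 = 9.4 months, a little shorter than the stated 10 to 11 months. Eleven months would imply 300/11 = 27.3 per month.

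The look is triggered by randomisation, no recruitment pause is stated, in-hospital outcomes run to discharge, and vital status is sought at day 30. With a lag of L months for follow-up and data cleaning, the number left is 150 − rate × L. The lags below are assumptions.

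| Lag before results are known | 32 per month | 27.3 per month |
| --- | --- | --- |
| 0 months | 150 | 150 |
| 1 month | 118 | 123 |
| 2 months | 86 | 95 |

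So 150 is a maximum for new enrolment. Some patients already randomised could still be in hospital, and the protocol does not allow that number to be estimated.

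**6. Would a trend be visible?** With about 75 per arm and complete outcomes, the planned rates give these expected primary events:

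- control: 75 × 0.25 = 18.8 to 75 × 0.30 = 22.5;
- high dose: 75 × 0.125 = 9.4 to 75 × 0.15 = 11.3.

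Power of an unadjusted two-sided 5% test at 75 per arm:

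- 25% versus 12.5%: null SE = √(2 × 0.1875 × 0.8125/75) = 0.0637; alternative SE = √((0.1875 + 0.1094)/75) = 0.0629; z = (0.125 − 1.960 × 0.0637)/0.0629 ≈ 0.00; power about 50%.
- 30% versus 15%: null SE = 0.0682; alternative SE = 0.0671; z = (0.150 − 1.960 × 0.0682)/0.0671 ≈ 0.24; power about 60%.

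If the planned effect is real, the SC would probably see a clear difference. This describes what would be seen and does not estimate bias.

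**The case against.** Several objections have force.

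- **The route to the sites is not documented.** A reader might infer that interim trends will pass from the SC to the bedside. The protocol does not say that SC members enrol or treat patients, and the roles and responsibilities section is absent from the text available for review. The material listed for centres is largely set-up material. This stands, so the point is one of risk.
- **The Charter may narrow access.** It is to be signed before the trial commences and is not shown. Section 4.4 also does not state in what form the SC receives the results. That is a reason to align the two documents, but a Charter should not have to override the protocol.
- **Trial size.** A reader might infer that the SC would resize the trial knowing the treatment effect. Section 4.3 gives the sample-size question to the DSMB, section 4.4 contains no resizing rule, and section 6.1 requires an approved formal amendment for any change.
- **Adverse events.** A reader might take the joint SC and DSMB review of adverse events as by-arm access. That sentence does not mention tabulation by arm, so no change to it is needed on this ground.
- **Contradiction.** Sections 4.3 and 4.4 do not strictly contradict each other, since exclusive access was never promised. The DSMB also keeps its right to stop for safety.
- **Endpoint mix.** Death, myocardial infarction and objectively confirmed thromboembolism are less open to influence than the ventilation components. That limits the exposure but does not remove it.

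**Conclusion.** The point holds as a weakness in who may see interim results. Section 4.4, read plainly, has a body with operational roles evaluate a between-arm comparison, and nothing elsewhere in the protocol restricts this.

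Up to 150 of 300 patients would be randomised after the look, or roughly 118 to 123 if results arrive one month later and recruitment continues at the rates implied by section 2.7.

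The conclusion rests on reading the evaluated results as arm-level, which section 4.4's own superiority and survival wording supports, and on the SC's roles as described in the protocol. It does not rest on any assumed overlap between SC members and site investigators.

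A reader might want a figure for the resulting bias. The protocol supports neither a size nor a direction, and any such number would only restate an assumed shift. The change is worth making because the safeguard is standard and cheap.

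**What to change.** Amend section 4.4 so that arm-level interim results, for efficacy and safety, go only to the DSMB. The SC should receive two things:

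- the DSMB's recommendation to continue, modify or stop the trial;
- the clinical-worsening rate pooled over both arms, for checking the sample-size assumptions.

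Align the DSMB Charter with this wording. The sentence on AE review can stay as it is.

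The cost is a few lines of text, with no added patients or procedures. The downside is that the SC will not see by-arm data until the end, unless the DSMB recommends stopping or modifying the trial. Having the DSMB tables prepared by a statistician outside the trial team would be a further safeguard. It could need extra staff, and this fix does not depend on it.

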| **Statistical Considerations**  **& Sample Size** | **Statistical Considerations**  The efficacy will be assessed by estimating the difference between the two treatment arms in the proportion of participants experiencing clinical worsening during their hospital stay.  Safety will be assessed by estimating the difference between the two treatment arms in the proportion of participants who experience at least one bleeding event (major or non-major) during their hospital stay.  Relative risk (RR) will be used as measure of association, which will be reported with its 95% confidence interval.  The differences between the two arms in the variation of:   1. D-dimer level 2. Plasma fibrinogen levels   3) Mean platelet Volume  4) Lymphocyte/Neutrophil ratio  5) IL-6 plasma levels  at 3 time points (at randomization, at 48 hours and 96 hours) will be assessed.  These outcomes will be compared by using their mean values and summary indicators.  Overall survival, survival free from any cardiovascular event, such as Acute Myocardial Infarction [AMI], Objectively confirmed, symptomatic arterial or venous thromboembolism [TE] and survival free from need for either non-invasive or invasive mechanical ventilation will be also estimated. They will be reported by using Kaplan-Maier curves and compared by using hazard ratio (HR).  **Sample size**  300 participants will be needed to detect a relative reduction of 50% of clinical worsening. We hypothesized that the percentage of participants who experience clinical worsening in the LMWH low dose group would be around 25-30% and set an alpha error of 0.05 and beta-error of 0.20. | |
| **Treatment Schedule** | **Control group (Low Dose):** Enoxaparin (Inhixa®) 4000 IU subcutaneously once daily.  **Intervention group (High dose**): Enoxaparin (Inhixa®) 70 IU/kg subcutaneously twice daily.  Participants will receive the dose of Enoxaparin according to the protocol until the occurrence of at least one of the following events:   1. One of the events included in the primary outcome 2. Hospital discharge 3. Any adverse events and clinical condition requiring interruption of the scheduled intervention according to the judgement of the physician in charge | |

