**2.6 SAMPLE SIZE**

The target sample size is based on the hypothesis that LMWH administered at high doses versus low doses will significantly reduce the risk of clinical worsening. The overall sample size in this study is expected to be 300 with a 1:1 randomisation ratio. Assuming an alpha of 5% (two tailed) and a percentage of patients who experience clinical worsening in the control group being between 25% and 30%, the study will have 80% power to detect at least 50% relative reduction in the risk of death between low and high doses of heparin.

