**4.2 Statistical Methods**

All patients enrolled in the study will be entered in the full analysis set independently of his/her treatment time. The intention to treat population will be considered for primary analysis. A descriptive statistical analysis will be carried out to summarise every relevant variable. At baseline, categorical data will be summarised by using counts and percentages, whilst continuous variables will be presented using the number of patients, mean, standard deviation, median, minimum, and maximum. Comparison between binary outcomes will be performed by using Relative Risks (RRs), whereas for continuous data, the difference of means (DMs) will be used. Comparisons involving time to event data will be displayed by using Kaplan-Maier survival curves and summarised by Hazard Ratios (HRs).

All measures of association will be presented with their 95% confidence interval. A result will be considered as statistically significant if its p-values will be less than 0.05 (5%).

The analyses will be performed by using STATA software.

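### Section 4.4 lets a 'significant' survival difference at half the sample end the comparison without an adjusted boundary; read with the protocol's only significance level, the overall error is 8.3% or more, not 5%

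*Protocol*

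**What the plan says.** Section 4.4 sets the timing: "an interim analysis is planned after the randomisation of 150 patients (50% of sample size"). The stated aims are safety monitoring and a check of the sample-size assumptions. The section then adds that the look may show substantial superiority of one arm, and attaches a consequence: "in case of significant differences in survival among the groups, all patients will be switched to the most promising treatment". On who sees the data: "The obtained results will be evaluated by the DSMB and by the SC".

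Section 4.2 holds the only significance criterion in the protocol, worded for any result: "A result will be considered as statistically significant if its p-values will be less than 0.05 (5"%). Section 2.6 sizes the trial "Assuming an alpha of 5% (two tailed") and makes no allowance for a look.

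The primary efficacy endpoint in section 2.4.1 is composite clinical worsening. Death is one of its five components, and in-hospital death alone is a secondary endpoint in section 2.4.2. Section 2.6 mixes the two: it takes "a percentage of patients who experience clinical worsening in the control group being between 25% and 30"% and then says "the study will have 80% power to detect at least 50% relative reduction in the risk of death". The synopsis has "300 participants will be needed to detect a relative reduction of 50% of clinical worsening". Section 4.3 gives the DSMB the right to stop for safety reasons and mentions no stopping for efficacy.

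**The concern.** A rule that moves every patient to one arm when a difference is significant is an efficacy stopping rule, whatever else the look is for. If significant means p<0.05 at the look and again at the end, the trial has two chances of a false positive and has paid for one.

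The rule also acts on survival, which is neither the primary endpoint nor the quantity that the synopsis powers. A chance imbalance in deaths among 75 patients per arm could therefore close the trial before its primary question is answered. If the trial continues instead, the Steering Committee of an open-label study has seen the comparative results.

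**Working it through.** **1. The plan's own sample size.** Inputs from section 2.6: control rate 25-30%, 50% relative reduction, two-sided alpha 0.05, power 80%, 1:1 allocation. With p̄ the mean of the two rates,

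n per arm = [1.96·√(2p̄(1−p̄)) + 0.8416·√(p1(1−p1) + p2(1−p2))]² / (p1−p2)².

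- 25% v 12.5%: 151.9, so 152 per arm and 304 in total. Power at 150 per arm is 79.5%.
- 30% v 15%: 120.5, so 121 per arm and 242 in total. Power at 150 per arm is 87.9%.

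The stated 300 is reproduced, within rounding, at the 25% end. It spends the full two-sided 5% on one final test.

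**2. Same endpoint at both looks, each at 0.05.** The information fraction is t = 150/300 = 0.5, so corr(Z1, Z2) = √0.5 = 0.707. Overall error = 1 − P(|Z1|<1.96 and |Z2|<1.96) = 1 − 0.9169 = **8.3%**. The look is triggered by randomisation, not completed follow-up, so t may be lower. The error is 8.5% at t = 0.45, 8.6% at 0.40 and 8.9% at 0.30.

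**3. Death at the interim, composite at the end.** The protocol gives no mortality rate for this comparison, so I assume death pd = 5-20% and take the composite pc = 25-30%. Because death is a component of the composite, the correlation of the two statistics at the same look is ρ = √[pd(1−pc) / (pc(1−pd))]. Across looks it is ρ·√0.5.

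| pc | pd | ρ | ρ·√0.5 | Either test falsely significant |
|---|---|---|---|---|
| 25% | 5% | 0.397 | 0.281 | 9.5% |
| 25% | 10% | 0.577 | 0.408 | 9.3% |
| 25% | 20% | 0.866 | 0.612 | 8.7% |
| 30% | 5% | 0.350 | 0.248 | 9.6% |
| 30% | 10% | 0.509 | 0.360 | 9.4% |
| 30% | 20% | 0.764 | 0.540 | 9.0% |

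The ceiling, for independent tests, is 1 − 0.95² = 9.75%. A simulation of binary endpoints (75, then 150 per arm, 400,000 runs) agrees: 9.1-9.6% over selected pairs in these ranges. These are chances of a false conclusion on either endpoint. The final composite test by itself is made once, at about 5%.

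**4. Candidate boundaries at t = 0.5.**

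- Haybittle-Peto, interim 0.001 and final 0.05: 5.02% on one endpoint. With survival at the interim and the composite at the end, it is at most 1 − 0.999 × 0.95 = 5.1%.
- O'Brien-Fleming, |Z| of 2.797 then 1.977 (p 0.0052, then 0.048): 5.00% on one endpoint.

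**5. Chance of crossing at the interim under the design effect** (composite, 75 per arm).

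| Interim level | 25% v 12.5% | 30% v 15% |
|---|---|---|
| 0.05 | 50% | 60% |
| 0.0052 | 20% | 27% |
| 0.001 | 9% | 13% |

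At 150 per arm, lowering the final level from 0.05 to 0.048 takes power from 79.5% to 79.0% (25% control rate) or from 87.9% to 87.5% (30%).

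**The case against.** The strongest reply is that section 4.4 gives no p-value. The 0.05 is carried over from section 4.2, and a numerical boundary often sits in a DSMB charter or SAP. Section 4.3 promises a charter before the trial commences, and neither document is at hand. This stands as a limit: the 8.3% is conditional on reading the text as written. It does not remove the point, because the protocol itself ties a trial-ending action to the word 'significant' and defines that word only once.

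A reader might infer that the primary test's own type I error rises to 9-10%. The documents do not support that. If the interim tests survival only, the composite is still tested once at 0.05, and 8.7-9.6% is the chance of an error on either of two endpoints. All these figures are two-sided, so a false claim for the high dose is about half of each, roughly 4-5% against 2.5%.

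The choice of test also matters. Fisher's exact test on death at 75 per arm has a true level of about 1.5% (5% mortality) to 3.1% (20%), which would lower the combined figure to at most 5% + 3.1% = 8.1%. The protocol names no test.

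Three further inferences should not be drawn:

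- **That the latest patients have no outcome at the look.** At 40 × 80% = 32 enrolments a month (section 2.7), about 32 of 150 would have under 30 days of follow-up. The synopsis defines worsening over the hospital stay, and a time-to-event analysis is planned, so partial follow-up is usable.
- **That an early stop must overstate the planned effect.** On the composite, nominal significance at 75 per arm needs an observed relative risk near 0.5, which is the design effect itself.
- **That Steering Committee access will change decisions on CPAP or NIV.** Treating staff already know the allocation. Access is an avoidable risk, not a demonstrated bias.

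**Conclusion.** The point holds in conditional form. Section 4.4 states an efficacy rule that ends the comparison, section 4.2 supplies the only level, and section 2.6 spends the whole 5% at the end.

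Followed literally, the overall two-sided error is 8.3% on a single endpoint at half the information. For death followed by the composite, the chance of any false efficacy conclusion is about 8.7-9.6%, with a ceiling of 9.75%, while the final composite test alone stays at or below about 5%. These figures assume an interim level of 0.05, normal-approximation tests and, for the second, mortality of 5-20%.

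Separately, and without any assumption, the passages on the deciding endpoint (survival or clinical worsening) and on the grounds for stopping (efficacy in 4.4, safety only in 4.3) do not agree and must be reconciled.

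**What to change.** In section 4.4:

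- State an efficacy boundary that holds the overall two-sided error at 5%, for example Haybittle-Peto (interim p<0.001, final 0.05) or O'Brien-Fleming (0.0052, then 0.048, on one endpoint).
- Name the endpoint to which it applies and make it consistent with section 2.4.1. Correct the death/worsening wording in section 2.6 at the same time. If the sponsor keeps survival for the interim, 0.001 then 0.05 still gives at most 5.1%.
- Say that the boundary governs early stopping for efficacy only. The DSMB's right to stop for safety in section 4.3 must not depend on it.
- Restrict comparative interim results to the DSMB. The Steering Committee would receive a recommendation, plus pooled event rates for the sample-size check.

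The text change is a few sentences, mirrored in the DSMB charter. The real cost is that an early efficacy stop becomes clearly less likely. Under the design effect on the composite, its chance falls from 50-60% at 0.05 to 20-27% at 0.0052 or 9-13% at 0.001. Final power and sample size are essentially unchanged.
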